### Definitions for solicited adverse events

Solicited adverse events include the systemic reactions of fever, irritability, nausea, vomiting, and rash. (Appendix D)

Definitions of Solicited AEs:

Fever: as reported by the mother/caretaker or the field worker taking axillary temperature of 38ºC (100.4ºF), recorded by digital thermometer. Severe defined as > 72 hours of fever after administration of zinc and/or ORS.

Irritability. Activity or behaviour deemed to be unusual in intensity or duration compared with child’s normal behaviour as reported by the mother/caretaker. Severe defined as > 72 hours of irritability after administration of zinc and/or ORS.

Nausea. Complaint of being nauseated in verbal children as reported by the mother/caretaker after administration of zinc and/or ORS.

Vomiting. An episode of vomiting will be defined as at least one episode of vomiting occurring within 60 minutes of zinc administration in a child previously stable and not having vomited for at least 60 minutes prior to receiving zinc. Severe defined as not being able to breastfeed or drink anything for > 72 hours after administration of zinc and/or ORS, as reported by the mother.

Rash. Unusual redness, texture or swelling of skin that was not present before administration of study drug. Severe defined as involving mucosal membranes at any time, or having a duration of > 72 hours after administration of zinc and/or ORS.

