In the villages/clusters randomized to home zinc, parents will be supplied with one 10-day blister pack of zinc and 3 satchets of ORS for each child in the house under 5 years of age. Zinc packs and ORS satchets will be given once every 2 months, regardless of whether the zinc was used in the previous month. Parents will be given instructions on how to use zinc and ORS at the beginning of the study and every 2 months thereafter when the zinc is given to them by a village reporter (a traditional birth attendant) or a community health worker. Parents in these villages/clusters will also be instructed to take their children to the clinic if they have diarrhea. They will be specifically instructed that taking zinc and ORS should not prevent them from taking their child to the clinic. Particular emphasis will be made that any child with diarrhea, *and* another symptom such as fever or cough, should definitely be taken to the clinic – that zinc is not adequate treatment for a child with fever or cough, who might need an antimalarial or an antibiotic. If the field worker on his biweekly visit finds out that the mother has given zinc to a child not meeting the diarrhea case definition, he will not tell the mother to stop the course of zinc. This is for several reasons. First, the field worker will not be medically trained and so will not be trained to apply the case definition of diarrhea. Second, diarrhea is a symptom taken by history, so that if the mother reports the child has diarrhea, the field worker will not really be able to assess the accuracy of that symptom. Third, there will be no adverse effects from the course of zinc – daily zinc supplementation regardless of illness has been shown to be beneficial in some studies (Zinc Investigators Collaborative Group 1999, Zinc Investigators Collaborative Group 2000). However, the field worker will encourage all mothers of children with diarrhea, especially those with fever, cough or another symptom, to go to the clinic to be seen by a clinical officer. The use of zinc for episodes of diarrhea will be evaluated on a biweekly basis based on the data collected by the field workers to assure that zinc is not being given alone when the child has other symptoms, such as fever and cough. If a significant number of mothers are giving zinc inappropriately without seeking care for other symptoms, further education in the use of zinc in the home will be given. Community health workers or village reporters, different from the field workers who do the biweekly visits, will make home visits every month during the first 3 months of the study to ensure that mothers understand the proper use of zinc and ORS for treatment of diarrhea. After the first three months, the village reporter or community health worker will visit the home every 3 months. On each home visit, the village reporter will ask some questions to assess whether mother is using zinc correctly (appendix L).

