## Solicited Adverse Events.

Solicited Adverse Events are potential side effects to the treatment of diarrhea, zinc and/or ORS that occur up to 24 hours after the last dose, and will be ascertained from the 3 and 7-day visits by the field worker using a standardized questionnaire (Appendix E). These may or may not be reportable incidents, depending on whether they meet the definitions below.

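### Solicited fever and irritability (and, in part, nausea) need not be new since the first dose, so symptoms of the presenting illness count as solicited adverse events and can be graded severe

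*Protocol*

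**What the plan says.** The protocol section Solicited Adverse Events describes these events as potential side effects of zinc and/or ORS "that occur up to 24 hours after the last dose". That fixes the end of the window; it does not say that the symptom must begin after the first dose.

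The section Definitions for solicited adverse events then treats the five symptoms differently.

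- Rash: "Unusual redness, texture or swelling of skin that was not present before administration of study drug".
- Vomiting: within 60 minutes of zinc, "in a child previously stable and not having vomited for at least 60 minutes prior to receiving zinc".
- Fever: "Fever: as reported by the mother/caretaker or the field worker taking axillary temperature", with a 38 °C threshold for the measured value. The severe grade is "Severe defined as > 72 hours of fever after administration of zinc and/or ORS", with nothing said about onset.
- Irritability: "Activity or behaviour deemed to be unusual in intensity or duration compared with" the child's usual behaviour, as reported by the caretaker. The severe grade is "Severe defined as > 72 hours of irritability after administration of zinc and/or ORS".
- Nausea: a complaint by a verbal child after zinc and/or ORS, with no requirement that it was absent before and no severe grade.

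**The concern.** A child given zinc as intended is already ill with diarrhoea. The protocol treats fever and irritability as features of that illness. Under Administration of zinc, parents in the home-zinc villages are told that a child with diarrhoea and "another symptom such as fever or cough, should definitely be taken to the clinic". Under Referrals, recent fever is a ground for referral, and restlessness or irritability is one of the listed signs of dehydration. Study site and population describes malaria transmission as perennial and high. So two of the symptoms most likely to be present before treatment are the two with no condition on onset.

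At stake is what the fever and irritability counts mean. If they include symptoms that preceded zinc, they partly describe the presenting illness, a modest effect of zinc is harder to see, and some illness is labelled severe. The counts could also differ between arms without any effect of zinc, if zinc is started at a different point of the episode at home than at the clinic.

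**Working it through.** The protocol states no rate for these events, so there is no figure to reproduce. The check is a clause-by-clause comparison, followed by one example and an illustration of scale.

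**1. Is a pre-dose condition stated?**

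| Event | Must be absent before the dose? | Severe grade |
| --- | --- | --- |
| Rash | Yes | Mucosal involvement, or more than 72 h after administration |
| Vomiting | In limited form: 60 minutes free of vomiting, previously stable | Unable to drink for more than 72 h after administration |
| Nausea | No; only reported after administration | None |
| Irritability | No; compared with normal behaviour, not with the state just before the dose | More than 72 h after administration |
| Fever | No | More than 72 h after administration |

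**2. Does another section supply the condition?** Solicited Adverse Events gives only the end of the window. Reporting of incidents has a relatedness test, but it applies to incident reports and not to the counting of solicited events. Appendix D records the data by day but states no counting rule. None of these closes the gap.

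**3. Can a pre-existing symptom reach the severe grade inside the window?** Zinc is given once daily for 10 days, so the last dose falls 9 × 24 = 216 hours after the first, and the window closes at 216 + 24 = 240 hours. That leaves ample room for 72 hours. Take a child with malarial fever from day 0 through day 5 who starts zinc on day 1. The whole days 2, 3 and 4 alone give 3 × 24 = 72 hours of fever after the dose, and the febrile parts of days 1 and 5 take it beyond 72. As written this is a severe solicited fever. Under a new-onset rule it is no event. Likewise, a dehydrated child who was irritable before zinc and is improving still has an irritability event.

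**4. Scale, on assumed inputs only.** Let b be the share of courses with fever present at the first dose and continuing after it, and e the share in which zinc itself causes fever, taken as independent. The counted rate is 1 − (1 − b)(1 − e). The documents give neither input. For b of 20% to 50% and e of 2%:

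- b = 0.20, e = 0: 20%; e = 0.02: 1 − 0.80 × 0.98 = 21.6%
- b = 0.50, e = 0: 50%; e = 0.02: 1 − 0.50 × 0.98 = 51%

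This shows only how a background rate would mask a small effect. It does not estimate b. If b is read instead as the share febrile at onset of diarrhoea, these rates are upper bounds, because only fever lasting past the first dose counts.

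**The case against.** The strongest reply is that calling these events potential side effects, and systemic reactions, already presupposes that exposure came first, and that recording symptoms whatever their cause and judging relatedness separately is a legitimate design. Part of this stands: a solicited event is not thereby declared causal. But if the general wording were sufficient, the explicit conditions for rash and vomiting would be unnecessary. Nor can field judgement be relied on to supply the rule, since Administration of zinc says that the field workers lack medical training.

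The contrast with vomiting should not be pressed too far. Its guard covers only 60 minutes, so vomiting from the illness some hours earlier does not prevent an event, and its severe grade repeats no pre-dose condition.

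A reader might infer several stronger things that the documents do not support.

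- *That there is no untreated background at all.* Follow-up of cases of diarrhea applies to every new episode found at home or in the clinic, whether or not zinc was taken, and Appendix D has a daily row for zinc. Justification for the study says that most children with diarrhoea do not reach a health facility, so some episodes in the clinic-only villages will go without zinc. That background exists, but it is self-selected and not randomised.
- *That the arms will differ.* The documents give no start times for zinc within an episode, so a difference is possible and not established.
- *That safety reporting is compromised.* Reporting of incidents requires an event to be serious, unexpected and at least as likely due to zinc as to anything else. A severe grade on fever meets none of these by itself.
- *That a planned result is damaged.* No stated objective, and nothing in Data Analysis, uses solicited-event rates.

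**Conclusion.** The point holds as an inconsistency within the safety definitions. Fever and irritability, and in part nausea, lack the condition that rash has in full and vomiting has in limited form, and the severe grade for fever and irritability ignores onset. Applied as written, symptoms already present at the first dose are counted and can be graded severe, so those counts partly measure the presenting illness.

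The size cannot be obtained from the documents; the 20% to 50% background and the 2% excess used above are assumptions. The consequence is confined to the solicited-event counts and their severe grades. The primary outcome is unaffected and incident reporting is largely protected. The correction is worth making because it is cheap and because settling the rule beforehand avoids choosing it after the data are seen.

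**What to change.** Count fever, irritability and nausea as solicited events only if the symptom was absent before the first dose of that course, or recurred after a symptom-free day. Start the 72 hours for severe fever and severe irritability from that onset. The rash definition is the model.

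The cost is one sentence in each definition and a short derivation. Appendix D already has daily rows for zinc taken, fever, and irritability or restlessness, so no new data are needed for those two. It has no nausea row, so for nausea only the wording can be aligned. Because the grid is by calendar day, the rule should also say how a symptom first recorded on the day of the first dose is counted.

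There are two downsides. Worsening of a symptom already present would be kept only in the daily record and not as a solicited event. Illness that begins after the first dose, such as a new malarial fever during the 10-day course, would still be counted, so the background is reduced and not removed. The change concerns counting only and leaves treatment and referral as they are.

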### Reporting of incidents

The latest CDC guidelines for reporting of incidents associated with the study will be followed. Reportable incidents fall into four categories.

- Unanticipated problems involving risks to subjects or others
  - Including serious, unexpected, and possibly related adverse events
  - Other unanticipated problems involving risks to subjects
- Breaches of protocol and other examples of noncompliance with protocol or IRB requirements
- Premature suspension or termination of study
- Other incidents specified in the protocol (none apply here) or requested by IRB

Not all adverse events will require an incident report. Adverse events requiring an incident report must be meet all 3 criteria of being serious, unexpected, and possibly related adverse events. Serious AEs in the context of this study result in death, are life-threatening, result in inpatient hospitalization, or cause permanent disability. Unexpected AEs refer those that have not been observed before with this intervention. Expected AEs from the intervention should be clearly defined in the consent form. For this study, vomiting after the first dose of zinc is an expected AE that has been observed before. However, protracted vomiting would be unexpected. A reportable AE must be at least possibly related to the study intervention, zinc. That is it must be at least as likely to have been due to zinc as to other causes.

The procedure for reporting incidents is as follows. An Incident Investigation Form (Appendix F) will be initiated by the field supervisor, clinical officer or study coordinator upon notification of a possible incident. It will be completed by the PI, who will determine if it is a reportable incident. In the case that the PI is not available (e.g. on leave, tdy, etc), a designated senior scientist at CDC/KEMRI will be asked to make this determination. If deemed a reportable incident, within 2 days of being notified of the incident, the incident should be reported informally by email to both CDC Human Research Program Office and KEMRI ERC with the protocol number, a statement that an incident has occurred, the site and nature of the incident. Within 2 weeks of being notified of the incident, the program staff, particularly the PI, should submit an incident form 0.1254 (Appendix G) to CDC HRPO and KEMRI ERC, which includes a description of the incident and actions taken. If the incident is a reportable adverse event, then an adverse event form (0.1254Sv1.0, Appendix H), which documents the type of adverse event, the outcome, the seriousness, and the relatedness to the study intervention.

After review of the documentation, CDC IRB will notify the PI through HRPO of any further actions to be taken. These actions could include requests for further information, changes to the protocol, suspension or termination of the study, or acceptance of the report and action already taken with no further recommended actions. KEMRI ERC will be informed of CDC IRB decisions and may provide addition recommendations for further actions, if necessary.

Identification of reportable incidents will be accomplished by study personnel. The PI and study coordinator will identify breaches of protocol. Reportable adverse events will come to the attention of the PI through the community interviewers during their follow-up visits after starting treatment for diarrhea or at any other time in their biweekly rounds. Also, the clinical officer in the clinics will report potential adverse events in children that he sees in the clinic.

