| Ethiopia | 6 days/wk x 6 months | RCT | Stunted and nonstunted | Growth | fever | Significant decrease in stunted, not nonstunted | Umeta, lancet 2000 |
| Burkina Faso | 6 days/wk x 6 months | RCT | From DSS | Malaria | fever | No Difference | Muller, 2001. |
| Lesotho | 90 days daily after admission | RCT | Children admitted with malnutrition | Multiple | fever | Decreased in zn group at 30, 60, 90 days | Makonnen, 2003 |
| Malaria |  |  |  |  |  |  |  |
| Burkina Faso | 6 days/wk x 6 months | RCT | From DSS | Malaria | Various ways | No Difference in incidence or severity | Muller O, 2001. |
| Uganda, Ghana, Tanz, Zambia, Ecuador | Supplement to treatment x 4 days | RCT, n = 1087 | Clinics | Malaria | fever, parasitemia, Hb | No difference | Zinc against Plasmodium group 2002. |
| Gambia | Twice weekly | ?, N=110 | Clinics | Malaria | clinical malaria | 32% reduction | Bates 1993. |

Other treatments, such as antimalarials, have been employed successfully using home-based treatment in Africa (Dunyo SK et al). There have been no studies of home zinc treatment for diarrhea in Africa. However, in Mali a program of community based zinc treatment of diarrhea by community health workers showed high acceptance and compliance by mothers (Ellis AA et al, 2006. Winch PJ et al, 2006). The major problem identified in the Mali project was that often mothers opted to give their children zinc alone when they had diarrhea accompanied by other symptoms, such as fever and cough, which required antimicrobial agents. (personal communication [name] from the nonpublished manuscripted entitled “Lessons learned in a pilot introduction of zinc treatment for childhood diarrhea in Bougoni District, Mali”). This problem was addressed and rectified by re-education of community workers and mothers. This point will need to be emphasized and monitored closely in any program of home-based zinc treatment of diarrhea.

Important questions remain regarding the use of zinc in subSaharan Africa.

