**Part 6: Adverse Events**

*To be filled out by the clinical officer:*

Is this clinic visit due to an unanticipated adverse event due to being in the zinc study?  Yes  No  Not sure

*Unanticipated adverse events include: anaphylaxis, severe rash or mucocutaneous reaction, continuous vomiting, sudden unexpected death without a clear cause in a previously well child, injury due to study procedure or participation.*

IF YES, MUST COMPLETE AN ADVERSE FORM AND REPORT TO PI.

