**Describe in detail the nature & timing of the INCIDENT (attach addendum if necessary):**

At the time of completing this report, determine status of INCIDENT?  Resolved  Not resolved  N/A

If event is resolved, determine status?  died  disability  resolved without disability  N/A

 Other ________________________________

If event is not resolved, determine status?  Hospitalized  participant home, event ongoing  N/A

 Other_____________________________

Part 3. Categorization/Rating *(To be completed by principal investigator)*

The likelihood that the INCIDENT was caused by the study is (definitions given at the end of form):

Definitely (direct association with research intervention)

Probably (more likely explained by research intervention than other cause)

Possibly (research intervention and other cause explain incident equally well)

Probably not (more likely explained by other cause than research intervention)

Not (clearly explained by another, documented cause)

CDC/IRB categorization of a reportable incident:

Unanticipated problems involving risks to subjects or others

Including serious, unexpected, and possibly related adverse events

Other unanticipated problems involving risks to subjects

Breaches of protocol and other examples of noncompliance with protocol or IRB requirements

Premature suspension or termination of study

Other incident defined as reportable in protocol or requested by IRB

Incident not reportable

Should the participant be withdrawn from study?  Yes  No

Has form 1254 been sent to CDC IRB?  Yes  No  N/A

_____________________ ___________

Signature of investigator Date

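### The relatedness test for reportable adverse events refers to zinc itself, so harm from home zinc replacing other care would normally fall outside it, and Appendix F applies a different standard

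*Protocol*

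**What the plan says.** Under Reporting of incidents, the protocol sets a cumulative rule: "Adverse events requiring an incident report must be meet all 3 criteria of being serious, unexpected, and possibly related adverse events". It defines two of the terms. On expectedness: "Unexpected AEs refer those that have not been observed before with this intervention". On relatedness: "A reportable AE must be at least possibly related to the study intervention, zinc", followed by the threshold that "it must be at least as likely to have been due to zinc as to other causes". The same section lists other reportable categories: other unanticipated problems involving risk, breaches of protocol, suspension or termination of the study, and incidents that the protocol specifies or the review board requests. The protocol states that it specifies none.

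The Background names a hazard of home supply. In the programme in Mali, "often mothers opted to give their children zinc alone when they had diarrhea accompanied by other symptoms, such as fever and cough", and the protocol says this must be watched closely. The section on administration of zinc has parents told that "zinc is not adequate treatment for a child with fever or cough, who might need an antimalarial or an antibiotic". It provides for a biweekly review of whether zinc is being given alone to children with other symptoms, with further education if this is common.

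The forms use other wording. Part 3 of Appendix F has a rating that begins "The likelihood that the INCIDENT was caused by the study is", with grades that set the research intervention against other causes. Part 6 of Appendix E asks the clinical officer "Is this clinic visit due to an unanticipated adverse event due to being in the zinc study" and gives examples. The introduction to Appendix H speaks of relation to the research procedures.

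**The concern.** A relatedness test should refer to whatever the trial randomises. Here that is not zinc against no zinc. Children in both arms are given zinc and ORS at the clinic, and the home villages also hold a supply that parents start themselves. Harm specific to the randomised difference therefore includes harm through behaviour: zinc is given at home, the child is not brought to the clinic, and another infection goes untreated. The protocol identifies this path itself, yet its reporting test asks only whether zinc was the likely cause.

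At stake is what the two review committees are told during the trial. If such deaths or admissions occurred in home villages, the adverse-event route would not require them to be reported as related. The results are meant to inform the Ministry of Health's decision on community roll-out, for which this is a central safety question.

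**Working it through.** No arithmetic applies. The check takes one event, a death or admission from malaria or pneumonia in a child given home zinc alone, through each criterion and route.

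**The three criteria (Reporting of incidents)**

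1. *Serious.* Met. Death and inpatient admission are both in the protocol's definition.
2. *Unexpected.* Probably met. The definition turns on whether the event has been seen before with the intervention. The Mali experience is a behaviour; no death or admission is described. The protocol's example of an expected event is vomiting after the first dose. This criterion does not clearly block the report.
3. *Related.* Not met on a literal reading. Between zinc and the infection, the infection is the likelier cause. This is the criterion that blocks.

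**The other routes**

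4. *Other unanticipated problems.* This category does not carry the zinc test, so it is open. It fits awkwardly, because the protocol anticipates the problem. Under the reporting procedure, the principal investigator (or a designated senior scientist) decides.
5. *Incidents specified in the protocol.* Empty, by the protocol's own statement.
6. *Request by the review board.* Possible, but not automatic.
7. *Appendix E, Part 6.* The question covers participation in the study, which is wider than zinc. The only death among the examples is a sudden one with no clear cause in a child who was well before, which does not describe death from a recognised infection. The form is also completed at a clinic visit, whereas the hazard is that no visit takes place.

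**Text against form**

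| Place | Cause is rated against | Cut-off for possibly related |
| --- | --- | --- |
| Reporting of incidents | Zinc | At least as likely as other causes |
| Appendix F, Part 3 | The study; the research intervention | Explains the incident as well as another cause does |
| Appendix H, introduction | The research procedures | Not defined there |

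The cut-off in the first two rows is the same, equal likelihood. The referent differs. With the research intervention as referent, an investigator can ask whether home supply led to care being forgone, and may grade the event as possibly related. With zinc as referent, the same facts give a negative answer. One event can thus be related on the form and not reportable under the text.

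**What is monitored**

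The biweekly review under administration of zinc measures the behaviour and responds with education. It is not tied to any death or admission.

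**The case against.** The strongest reply is that the event would not be lost. An Appendix F form is opened for any possible incident before reportability is decided. It has boxes for death and hospitalization and asks whether zinc was taken in the preceding week. The category of other unanticipated problems and the review board's power to ask for reports both remain. The behaviour is watched through biweekly visits, visits by separate village staff and the questions in Appendix L. Sick children are referred and treated free of charge, and clinic visits and antibiotic use are compared between groups. The question in Appendix E is broadly worded, its list is of examples, and it allows an answer of not sure.

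All of this stands, and it limits the point. A reader might infer that such events can never be reported. The routes above do not support that. A reader might also infer that the event fails on expectedness as well as on relatedness, but the protocol reports the Mali behaviour and not resulting deaths as seen before. Nor is it right that deaths could not be seen by arm: arm follows from village, death ends a child's person-time, and records link to the demographic surveillance system by child identifier. The protocol states no comparison of deaths or admissions by arm, but an analysis plan may hold one, so its absence is not counted as a defect here.

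The reply does not remove the mismatch. The optional routes rest on judgement, and the mandatory one uses a referent that leaves out the hazard the protocol names. An investigator could read harm due to zinc generously, so as to include zinc given in place of care, but reportability should not turn on that choice.

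**Conclusion.** The point holds in this form: the relatedness test is tied to zinc as a product, while the randomised difference is home supply. Serious events from zinc replacing other care would normally fall outside mandatory adverse-event reporting and depend on the investigator's judgement or a board request. Appendix F applies a different standard to the same event, and the two need reconciling whatever an analysis plan contains.

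No size in events is given. The protocol reports infant mortality of 120 per 1,000 live births but no rate for children aged 2 to 59 months, and nothing on the share of deaths that would follow forgone care. Any count would rest on assumption.

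The conclusion assumes a literal reading of zinc in the relatedness sentence, and that a death from malaria or pneumonia would be attributed to the infection. It does not depend on whether ORS is also held at home in the comparison villages. The Benefits paragraph suggests that it is, while the design figure says otherwise; home zinc differs between arms either way. This should be fixed, but it does not undermine the trial's design.

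**What to change.** 1. In Reporting of incidents, define relatedness to the intervention as randomised, namely home supply of zinc and ORS in addition to clinic treatment. State that this includes delayed or forgone care. Use the same definition in Appendix F and apply it identically in both arms.
2. Add delayed or forgone care to the examples in Appendix E, Part 6.
3. As a low-cost recommendation, tabulate all deaths (through the link to the demographic surveillance system) and all known hospital admissions by arm, regardless of attribution. The link's stated use is at present demographic, so this use should be added. Admissions may be incompletely captured: Appendix C has rows for clinic visits but none for admission, and Appendix E records only referral to hospital. The table should say so.

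A blanket rule that no serious event after home zinc without a clinic visit may be excluded is not advised. It would bear almost only on the home villages and make reporting unequal between arms.

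The cost is amendment wording, one added example on a form and a simple table. The downside is that the investigator will have somewhat more incident forms to review. No clinical rule changes.
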